### Measures/outcomes

Socio-demographic measures assessed at T0 - T3 include mother's age, education, occupation, ethnicity, number of children, household status, housing situation, household economy, substance abuse, and breastfeeding expectations. All study measures and outcomes are presented in Table 1.

**Table 1 Tab1:** The timing of the administration of measures

		T0	T1	T2	T3	T4	T5
Parent measures							
Socio-demographic measures	Age, education, etc.	√		√	√		
Pregnancy reflective functioning	PRFQ-P		√				
Well-being	WEMWBS	**√**		√	√		
Anxiety and depression	HADS	**√**					
Overall health parent and satisfaction	Health and satisfaction	**√**		**√**	√		
Breastfeeding duration				**√**	**√**		
Education and job expectation		√			**√**		
Family budget		**√**		**√**	**√**		
Network	Confidants, support	**√**		**√**	**√**		
Worry		**√**		**√**	**√**		
Use of alcohol, drugs, and medicine use		**√**		**√**	**√**		
Smoking		**√**		**√**	**√**		
Experiences in close relationships	ECR-R	**√**					
PTSD symptoms	PTSD-8		√				
Childhood trauma questionnaire	ACE10		√				
Postnatal depression	EPDS			**√**	**√**		
Being a mother	BaM-13			√			
Parental reflective functioning	PRFQ				**√**		
Parental stress	PSS				**√**		
Anti-conception				**√**	**√**		
Experience with cross-sectional collaboration				**√**	**√**		
Child measures							
Social-emotional development	ASQ-SE2			**√**	**√**		
Child development	ASQ-3			**√**			
Bayley Scales of Infant Development	BSID-III				**√**		
Relationship measures							
Learning activities	Singing, reading				**√**		
Mother and Baby Interaction Scale	MABISC				**√**		
Coding interactive behavior (video)	CIB			**√**	**√**		
Teacher measures							
Social-emotional development	SEAM					**√**	**√**

#### Baseline measures

In addition to the socio-demographic measures, we include the following measures at baseline to assess the initial level and to account for them as possible moderators or confounders in the effect analyses.

Prenatal Parental Reflective Functioning Questionnaire (P-PRFQ) [61] is a 14-item measure of parental reflective functioning of the pregnant woman’s ability to mentalize. The P-PRFQ is an adaption of the PRFQ [62] and consists of three subscales: opacity of mental states (4 items), reflecting on the fetus-baby (3 items), and dynamic of mental states (5 items). Cronbach’s alpha is 0.77 for the total score and 0.69–0.77 for the three subscales. Responses are on a Likert scale ranging from 1 to 7 with three different scalings: (1) high-low where 7 = optimal PRF and 1 = low PRF, (2) low-high where 1 = optimal PRF and 7 = low PRF, and (3) middle where 4 = optimal PRF and 1 and 7 = low PRF. Scores are summed to a total score ranging from 7 to 98.

Hospital Anxiety and Depression Scale (HADS) [63, 64] is a 14 item measure of anxiety and depression. HADS consist of the two subscales “anxiety” and “depression.” The two subscale scores are summed and range from 0 to 21, where low scores indicate less anxiety and depression.

Experiences in the Close Relationship Scale-Short Form (ECR-S) [65] is a 12-item measure of adult attachment consisting of the two subscales “anxiety” (fear of abandonment and a craving for interpersonal closeness) and “avoidance” (fear of intimacy and interpersonal dependency). Each subscale is scored by summing the items and ranges from 1 to 42, where low scores indicate better attachment.

Adverse Childhood Experience (ACE) Questionnaire is a 10-item measure developed for the ACE study to identify childhood experiences of abuse and neglect. Reponses are yes or no. The total score is summed, and the total range is 0–10 where 0 indicates no experience with childhood abuse and neglect.

PTSD-8 [66] is an 8-item measure of posttraumatic stress disorder (PTSD) symptoms, including intrusion, avoidance, and hypervigilance. The total score is the sum of the items and the range is 8–32, where a low score indicates less PTSD.

#### Primary outcome

The primary outcome is maternal sensitivity measured by the Coding Interactive Behavior (CIB) instrument [67] at child age 12 months. The main hypothesis is that mothers in the intervention group will have a higher level of parental sensitivity (a CIB composite) than mothers in the control group. Maternal sensitivity is a subscale of the CIB. The CIB is a global rating system for social interactions that includes 22 parent codes, 16 child codes, and 5 dyadic codes rated on a scale of 1 to 5 which can be aggregated into the following composites: sensitivity, intrusiveness, limit setting, involvement, withdrawal, compliance, dyadic reciprocity, and dyadic negative states. The CIB is coded based on a 6-min mother-infant free play interaction recorded in the home or at another location if preferred by the family. The CIB system has been validated as an assessment measure in multiple studies of mother-child interactions in both normative and high-risk populations and shows stability over time, predictive validity, and adequate psychometric properties [67–71]. Mother-infant interactions are coded by reliable coders blind to treatment allocation. The inter-coder agreement will be calculated on a 10% randomly selected subset of the sample.

#### Secondary outcomes

The parent-child relationship will be measured by the remaining composites of the CIB: intrusiveness, limit setting, involvement, withdrawal, reciprocity, and negative states.

The short version of the Warwick-Edinburgh Mental Well-being Scale (WEMWBS) [72, 73] is a 7-item measure of maternal mental health. A total score is calculated by summing the 7 items and converting the raw score according to a published conversion table. Raw score and converted score range from 7 to 35. A high score indicates better maternal mental health.

Ages and Stages Questionnaire-Social Emotional 2 (ASQ:SE-2) [74] is a measure of child social-emotional development. The ASQ:SE-2 consists of the following seven subscales: self-regulation, compliance, social-communication, adaptive functioning, autonomy, affect, and interaction with people. Items are summed to a total score ranging from 0 to 150 (3 months 15 items) and 0 to 260 (12 months 26 items). A low score indicates better development. Cronbach’s alpha ranges from 0.71 to 0.91. Concurrent validity ranges from 71 to 90%. Sensitivity ranges from 78 to 84%, and specificity ranges from 76 to 98% [75].

Ages and Stages Questionnaire 3 (ASQ:3) [76] is a 30-item measure of child developmental progress. ASQ:3 consists of the following five subscales: communication, gross motor, fine motor, problem-solving, and personal-social. Cronbach’s alpha ranges from 0.67 to 0.85 for the five subscales for the version for children aged 3 months [77]. Items are summed to a total score ranging from 0 to 300 and a low score indicates better development.

Edinburgh Postnatal Depression Scale (EPDS) [78, 79] is a 10-item measure of depression symptoms. Items are summed to a depression total score ranging from 0 to 30. A low score indicates fewer depression symptoms.

Being a Mother (BAM-13) [80] is a 13-item measure of a woman’s satisfaction and experience with being a mother. Items are rated on a 4-point scale (no, hardly ever, no, not very often, yes, some of the time, yes, most of the time). Items are summed to a total score ranging from 0 to 39. A low score indicates higher satisfaction.

Parental Reflective Functioning Questionnaire (PRFQ) [62] is an 18-item measure of parental reflective function or mentalization. The PRFQ consists of three subscales where items are summed and subscale scores range from 6 to 42: (1) Pre-Mentalizing Modes (PRFQ-PM) 6 items (a low score indicates better function), (2) Certainty about Mental States (PRFQ-CMS) 6 items (a high score indicates better function), and (3) Interest and Curiosity in Mental States PRFQ-IC 6 items (a high score indicate better function).

Activities with the child consist of 4 items measuring parent and child interaction through activities such as singing and reading. Items are summed to a total score ranging from 4 to 24. A high score indicates more interaction.

The Parenting Stress Scale (PSS) [81, 82] is an 18-item measure of parenting stress that is rated on a five-point scale (strongly disagree, disagree, undecided, agree, strongly agree). The PSS consists of two subscales: parental stress (items 3, 4, 9, and 10–16) and lack of parental satisfaction (items 1, 2, 5, 6, 7, 8, 17, and 18). When scoring the subscales, LPS items are reversed, and item responses are dichotomized into 0 (strongly disagree and disagree) and 1 (undecided, agree, and strongly agree), and items 2 and 11 are left out. Scores are then summed to subscale scores each ranging from 0 to 9 (PS) and 0–7 (LPS), where a low score indicates less stress and higher satisfaction.

The Mother and Baby Interaction Scale (MABISC) [83] is a 10-item measure of the mother-infant relationship that is rated on a 5-point Likert scale (always, most of the time, occasionally, not often, never). Items are summed to a total score ranging from 0 to 40, where a high score indicates a better relationship.

Bayley Scales of Infant and Toddler Development 3rd Edition - Screening Test (BSID) is a standardized norm-based test widely used to assess child development (Bayley, 2006). The BSID consists of three main subtests; the Cognitive Scale, which includes items such as attention to familiar and unfamiliar objects, looking for a fallen object, and pretend play; the Language Scale, which taps understanding and expression of language, for example, recognition of objects and people, following directions, and naming objects and pictures; and the Motor Scale, which assesses gross and fine motor skills such as grasping, sitting, stacking blocks, and climbing stairs. The cognitive scale assesses memory and problem solving, exploration and manipulation, object relatedness, and sensorimotor development. Raw scores for each subscale are converted into scaled scores (range 1–19, M = 10, SD = 3), and a composite score (M = 100, SD = 15) can be derived from the scaled score for cognitive development, and the sum of the two language-scaled scores. The test will be administered at T3 by trained psychology students supervised by an experienced and trained psychologist.

The mothers will also be asked single items about overall health, life satisfaction, breastfeeding intention, breastfeeding duration, use of birth control, supportive network, loneliness, and how they experience the cross-sectional collaboration between the professionals. If the mother is not employed, she will be asked questions about the indicators for progression toward employment (belief in own skills, mastery of health, and work identity). These items were developed in the employment indicator project [84].

At T4 when the child is 2 years old, the child’s primary teacher in the daycare center will fill out the Social-Emotional Assessment/Evaluation Measure (SEAM) [85]. SEAM is a measure of child social-emotional development consisting of 35 items covering ten benchmarks: empathy, healthy interactions, expression of emotions, regulation of socio-emotional responses, cooperation, sharing and engaging, regulation of attention and activity level, independence, self-image, and adaptive skills. Items are rated on a 4-point scale (very true, somewhat true, rarely true, and never true) plus one column to indicate “concerns” and a column to indicate whether this behavior should be an “intervention goal.” Items are summed to a total score ranging from 0 to 105 (toddler) and a low score indicates better development. In a Danish representative sample of children assessed by the child care teachers Cronbach’s alpha ranges from 0.82 to 0.91 for the toddler version [86].

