#### The FACAM intervention

The FACAM intervention consists of assigning a specific support person (FACAM person in the following) to each pregnant woman in the intervention group, a person expected to hold this contact until school-age of the child. The intervention is flexible and tailored to each woman’s individual needs. Theoretically, the intervention builds on theories on how to reduce inequality in health and mentalization theory [56, 57] The idea is that if a pregnant woman or mother has access to practical help and support from a professional she trusts, then she can focus more on parenting the child. There is no strict manual for the intervention but guidelines are specifying different tasks that the FACAM person should address with the participant and how often they should be in contact. The tasks include attending with the participant at healthcare and/or social care visits during pregnancy and after birth or participating in consultations with the midwife, general practitioner, social worker, or job consultant. The tasks also include extra home visits or telephone calls to support the family depending on their needs. Focus for contacts can be practical issues such as reminding the family of inoculations, guiding them on how to register the infant for daycare, but also conversations about the economy, family functioning, health, contraception, childhood upbringing, and mother-child attachment for example. The Danish guidelines are available from the corresponding author. An important task for the FACAM person is to guide and refer the family to appropriate support from the hospital, from child care services, or relevant third sector volunteer organizations. During pregnancy and the first year of the child’s life, the FACAM person can offer up to a total of 47 h of support to the family. Depending on the initial level of concern, all FACAM mothers are also offered either a group-based or an individual-based attachment-based course during pregnancy and the first months of the child’s life. Families with a low level of concern are offered eight 2-h sessions of the Circle of Security Parenting Groups Program (COS-P) from when the child is around 2 months old. Families with a medium or high level of concern are offered up to 50 h of individual sessions with a focus on attachment (including an attachment interview and a focus on mentalization). From when the child is 1 year and until it starts school at age 6, the FACAM person can offer up to 10 h of support to the family each year. It is the intention that the FACAM person is consistent over time. For shorter periods of absence, another FAMKO person will take over the contact with the family if necessary. New FAMKO persons will receive thorough training and support from the other FAMKO persons.

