When a mother has consented to participate, a research team member registers the participant and sends out the baseline questionnaire. When the participant has filled out the baseline questionnaire, the participant is randomized by a research team member to receive either FACAM or CAU (1:1). The randomization is conducted with the tool “OPEN randomize” in REDCap and the procedure is logged. The randomization sequence was generated by an independent data analyst before recruitment started. Participants are stratified into two groups according to the level of concern assessed by the healthcare professionals which is filled out when participants are invited to participate in the study (levels 1 and 2 are categorized as a high concern, and levels 3 and 4 are categorized as a low concern). When the participant is randomized, the researcher informs the participant and the project coordinator at the municipality about which group the participant is allocated to. The project coordinator at Odense municipality then allocates a FACAM-person to the intervention families prioritizing FAMKO persons with free capacity in the same geographical area. If a group of FAMKO persons with free capacity is under a lot of pressure due to, e.g., sickness, the coordinator will then usually allocate a FAMKO person from another group. After the FAMKO person is allocated, the intervention commences.

The consent form and other related documentation are given to participants are available from the authors on request. The study has no trial steering committee or data monitoring committee as this is not required for behavioral interventions [59, 60].

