#### Administrative data

When the children are 2 years old, we will retrieve data on all families from Danish administrative data such as the Population Statistics Register, the National Patient Register, the National Prescription Register, the National Health Insurance Service Registry, Oral Health Register, the Education Register and the Danish Rational Economic Agents Model (DREAM). With these data, we can examine outcomes such as vaccinations, child examinations at the general practitioner and dentist, use of social and health care services including emergency visits, use of medication, and information about housing, education, and labor market participation for the parents.

For both intervention and CAU families, we will also collect municipal data on what other interventions the family has been offered (including out-of-home care).

We use participants personal identification numbers to retrieve registered data.

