### Data analysis

The primary outcome (CIB parental sensitivity at 12 months) is tested using linear regression with robust standard errors since we are interested in the mean difference between the groups but do not expect a perfectly normal distribution of data. The treatment effect is estimated as a fixed effect using a binary indicator of treatment. A Wilcoxon rank-sum test will be used in the case of severe non-normality. Variables with indications (*p* < 0.1) of the differences between intervention and CAU groups at baseline are used as control variables. Missing data is handled using multiple imputations using all available baseline data. Secondary outcomes are analyzed following the same principles.

Additional exploratory analyses will be carried out in a mixed-effects regression framework. This allows for growth curve estimation. Two-sided tests with 0.05 significance levels are applied throughout.

In addition to the primary analysis, we will perform subgroup analyses to examine the potential differences between subsets of participants. Hence, we analyze the subgroups according to the following characteristics: primiparous or multiparous, education (high school or less versus more than high school), concern about the family (level 1/2 or level 3/4), provider (health visitor or family therapist), adult attachment style (ECR-S), initial trauma level (ACE < 3 or ACE ≥ 3), the initial level of reflective function (lowest 50% versus highest 50%), the initial level of depression or anxiety (clinical or not-clinical level), and attendance (dose).

The primary analysis will be based on the intention-to-treat (ITT) principle, aiming to include all participants in the arm they were originally allocated to irrespective of the amount of treatment received. Missing data is handled using multiple imputations using all available baseline data. Sensitivity analyses will be performed to investigate the potential impact of missing data, in particular, by using a pre-specified conservative multiple imputation strategy and a complete case analysis.

We do not expect that participants will be harmed by the study and therefore have no predefined stopping guidelines and no a priori planned interim analyses.

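### The employment-progression items go only to mothers not employed when surveyed, so a 12-month comparison of the arms would rest on a subset formed after randomisation

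*Protocol article*

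**What the plan says.** All references are to the protocol article.

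- **Who is asked.** Text under the heading "Secondary outcomes" introduces a set of single items and then a conditional block: "If the mother is not employed, she will be asked questions about the indicators for progression toward employment". The indicators are "belief in own skills, mastery of health, and work identity". The condition does not refer to baseline employment.
- **When.** That text gives no time point. The closest row of Table 1 (Measures/outcomes) is "Education and job expectation", ticked at T0 and T3.
- **Randomisation.** Under Procedures and randomization: "When the participant has filled out the baseline questionnaire, the participant is randomized by a research team member". T3 is when the child is 12 months old, so it falls well after allocation.
- **Link to the intervention.** The FACAM person's tasks include "participating in consultations with the midwife, general practitioner, social worker, or job consultant".
- **Analysis.** The Data analysis section applies the principles of the primary analysis to secondary outcomes: linear regression on a treatment indicator with robust standard errors, and multiple imputation from baseline data. The intention-to-treat sentence, written for the primary analysis, describes it as "aiming to include all participants in the arm they were originally allocated to irrespective of the amount of treatment received".
- **Other employment data.** Occupation is among the repeated socio-demographic measures (Table 1 ticks T0, T2 and T3). The Administrative data section plans register data for all families, including "information about housing, education, and labor market participation for the parents".

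**The concern.** A woman's T3 indicator score exists only if she is out of work at T3. That status arises after randomisation, and the support on offer includes job-consultant meetings, so it may differ between arms because of allocation. The women with scores in the two arms are then no longer two random samples of the same population.

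A woman who moves into work also loses her score on the measure of progress toward work. If FACAM helps more women into jobs, and those women would have scored well, its remaining non-employed group looks worse for that reason alone. A real benefit on this outcome could be reported as small or absent, and no effect on the indicators could appear as harm.

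**Working it through.** The article gives no figure for this outcome, so there is none to reproduce. The first step is structural; the rest only shows how large the effect could be.

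**1. Structure.** A score is observed at T3 only if the mother is not employed at T3. The handling available in the article does not change this:

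- Imputing employed mothers' scores from baseline data assumes that, given baseline, the score is unrelated to T3 employment. For an indicator of progress toward employment that is doubtful, and these scores are absent by design.
- A complete-case analysis is the selected comparison itself.
- Restricting to women not employed at T0 does not suffice alone, because those who find work by T3 are still not asked.

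**2. Model.** Let the score have SD 1 and correlation ρ with a normal employment propensity. A mother is employed when her propensity exceeds c, where p is the proportion employed in usual care and c = Φ⁻¹(1 − p). FACAM shifts propensity by s. With λ(x) = φ(x)/Φ(x), the difference among non-employed mothers is

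observed difference = (true score shift) − ρ[λ(c − s) − λ(c)].

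The second term is the bias. Assumed inputs, none from the article: p = 20% to 50%, employment gain under FACAM 5 to 15 points, ρ = 0.3 to 0.9.

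**3. A middle case.** Take p = 35%, FACAM 45%, ρ = 0.6. Then c = 0.385 and s = 0.260, so c − s = 0.126. λ(0.385) = 0.570 and λ(0.126) = 0.720. Bias = −0.6 × (0.720 − 0.570) = −0.09 SD.

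- True score shift 0: observed −0.09 SD.
- True shift ρs = 0.6 × 0.260 = 0.16 SD: observed 0.16 − 0.09 = 0.07 SD.

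With a 15-point gain, a true zero appears as −0.14 SD, and a true 0.23 SD as 0.09 SD.

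**4. Range.** Over the whole grid, a true zero appears as −0.02 to −0.23 SD. Where the score shifts in step with propensity, true differences of 0.04 to 0.41 SD appear as 0.01 to 0.21 SD.

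**5. False positives against FACAM.** With 136 per arm (320 × 0.85 / 2), a Welch t-test, 4,000 simulated trials, p = 35%, ρ = 0.6 and no effect on the score, two-sided type I error is about 9.6% for a 10-point gain and 15.4% for a 15-point gain, against a nominal 5%.

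**6. The extreme case.** Let score and propensity be the same variable (ρ = 1), with a true shift of 0.33 SD, a size borrowed from the sample size section for illustration only.

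| Employed, usual care | Implied employed, FACAM | Mean score, non-employed, usual care | Mean score, non-employed, FACAM | Observed difference | Share of 0.33 retained |
|---|---|---|---|---|---|
| 5% | 9% | −0.109 | 0.144 | 0.253 | 77% |
| 10% | 17% | −0.195 | 0.024 | 0.219 | 66% |
| 20% | 30% | −0.350 | −0.173 | 0.177 | 54% |
| 30% | 42% | −0.497 | −0.348 | 0.148 | 45% |
| 50% | 63% | −0.798 | −0.689 | 0.109 | 33% |

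The bias in SD units is proportional to ρ and shrinks as fewer women move into work. With the step 3 bias, a true 0.33 SD would appear as 0.33 − 0.09 = 0.24 SD, about 73% retained.

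**The case against.** The strongest reply is that the article never spells out this comparison. The items have no score, time point or contrast, the abstract's list of secondary outcomes contains no employment outcome, and scoring a skip-pattern item is usual analysis-plan material. Part of this stands: T3 collection is an inference from a Table 1 row whose label differs from the item description. But the items sit under the secondary outcomes heading, secondary outcomes are to be analysed as the primary is, and a progression measure taken only at baseline could not be an outcome. An analysis plan can define a different outcome, but it cannot recover answers that were never requested.

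A reader might infer that the branching rule contradicts the intention-to-treat statement. It does not do so directly: that sentence names the primary analysis and concerns analysis by allocated arm. It reaches this outcome only through the shared-principles sentence, which leaves a tension rather than a contradiction.

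A reader might also take it as established that FACAM removes its best-progressing women, or that half or more of a real effect would be lost. Neither is shown. The direction needs FACAM to raise employment by 12 months and the indicators to track employability, and the job consultant is only one of several contacts in a parenting intervention. If FACAM leaves employment unchanged, this differential selection largely disappears. Retention of 33% to 54% requires score and propensity to be identical and employment gains of 10 to 13 points.

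Finally, occupation and register data cover everyone, so a gain in employment itself could still be detected. That limits the harm and supplies the means of repair.

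**Conclusion.** The point holds, conditional on T3 collection. A comparison of the progression indicators among mothers not employed at T3 is conditioned on a post-randomisation status that FACAM may affect, and imputation from baseline data does not restore the randomised comparison. That conclusion needs no numerical assumption.

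The direction is against FACAM only if FACAM raises employment and the indicators follow employability. The size cannot be determined from the article. Under the stated assumptions the bias lies between about −0.02 and −0.23 SD, with −0.09 SD in the middle case; the larger proportional losses belong to the extreme model. The outcome is a minor secondary one and the result for maternal sensitivity is untouched. The change is worth making because it is cheap, not because the trial's main conclusion is at risk.

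**What to change.** 1. State when the progression items are collected, and whether a mother on leave from a job counts as employed; the article says neither.
2. Define the analysis set by employment status at T0, before randomisation.
3. For every woman in that set, use an outcome that exists whatever her T3 status. Either put the T3 items to all of them, or analyse employment at T3 (from the occupation item, or from the DREAM register if its records can be dated to 12 months), or an ordered outcome with employment as the top category above any indicator score.
4. Label any comparison limited to women not employed at T3 as descriptive.

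The cost is one change to the survey branching and one analysis-set definition. Extra items may fit employed women less well. An ordered outcome is harder to interpret, and placing employment on top is a value judgement to be stated openly for mothers of one-year-olds. Recruitment began in October 2018, so women recruited early may already have passed T3 under the existing branching. For them, employment at T3 or the ordered outcome needs no new contact, and using one of these for everyone avoids mixing two ways of collecting the items.

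### SEAM at age 2 needs a daycare teacher, daycare use may differ by arm, and imputation from baseline data alone may not correct for that

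*Protocol article*

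**What the plan says.** **Who scores.** In the protocol article, Secondary outcomes, the measure is timed "At T4 when the child is 2 years old", and the rater is the child's "primary teacher in the daycare center will fill out the Social-Emotional Assessment/Evaluation Measure (SEAM". Table 1 lists SEAM as a teacher measure at T4 and T5 and ticks no other child measure after T3. No second rater is named, and the text does not say whether a child without a daycare teacher counts as missing or as not applicable.

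**What FACAM offers.** The section on the FACAM intervention gives "guiding them on how to register the infant for daycare" as an example of the practical issues that contacts can cover. It also says "The intervention is flexible and tailored to each woman’s individual needs", so not every family need receive this help. Support continues beyond the first birthday: "the FACAM person can offer up to 10 h of support to the family each year". It therefore overlaps the year before T4.

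**How gaps are filled.** Under Data analysis, "Missing data is handled using multiple imputations using all available baseline data", and "Secondary outcomes are analyzed following the same principles". Sensitivity analyses for missing data are planned "by using a pre-specified conservative multiple imputation strategy and a complete case analysis".

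**The concern.** Being in daycare at age 2 is a post-randomisation state, and it determines whether a SEAM score can exist. If FACAM guidance leads some families to use daycare who would not otherwise have done so, their children are scored in the FACAM arm, while comparable children in the CAU arm are not.

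Imputation from baseline data treats an unscored child as similar to scored children with the same baseline values. For families selected for severe social or psychological difficulty, the reasons a child stays at home may well arise or change after baseline. The rule as stated also passes over the most relevant predictors that the trial collects: ASQ:SE-2 at 3 and 12 months, ASQ-3 at 3 months and Bayley at 12 months.

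At stake is the only child rating planned after 12 months. A real benefit could be partly hidden because more children with difficulties became visible to a teacher. If the extra children did better than the others, the error would run the other way.

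**Working it through.** The plan gives no figure for SEAM or for daycare use, so there is none to reproduce. Its sample-size figures concern maternal sensitivity and do not bear on this point.

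**Inputs**
- Children per arm: 160 planned × (1 − 0.15 dropout) = 136. Both numbers are in the article. The 15% was set when sizing the primary outcome, so carrying it forward to age 2 is an assumption.
- p0 and p1, the proportions in daycare under CAU and FACAM: not in the documents, assumed.
- d, the number of SD by which the extra FACAM daycare children score worse than the other scored children: not in the documents, assumed at 0.5 to 0.8.

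**Formulas (no true effect)**
- Extra children as a share of scored FACAM children: (p1 − p0)/p1.
- Bias in the scored-children contrast: (p1 − p0)/p1 × d.
- Standard error in SD units: √[1/(136·p0) + 1/(136·p1)].

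| p0 / p1 | (p1 − p0)/p1 | Bias, d = 0.5 | Bias, d = 0.8 | SE | Bias / SE |
|---|---|---|---|---|---|
| 0.90 / 0.95 | 0.053 | 0.026 | 0.042 | 0.126 | 0.21–0.33 |
| 0.85 / 0.92 | 0.076 | 0.038 | 0.061 | 0.129 | 0.29–0.47 |
| 0.80 / 0.90 | 0.111 | 0.056 | 0.089 | 0.132 | 0.42–0.67 |

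More extreme assumptions widen the range. With 0.95/0.97 and d = 0.25 the bias is 0.02/0.97 × 0.25 = 0.005 SD. With 0.70/0.90 and d = 1.0 it is 0.20/0.90 × 1.0 = 0.222 SD.

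**From complete case to imputation.** The table describes the scored-children contrast, which in this plan is the complete-case sensitivity analysis. Under imputation the same expression applies approximately, with d replaced by the part of the deficit that the imputation model does not explain:
- If baseline explains none of it, imputed values reproduce each arm's scored mean and the full bias passes through.
- If baseline explains all of it, the bias disappears.
- Adding the child's own T2 and T3 scores should reduce the unexplained part further.

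If p0 = p1 and the same kinds of families use daycare in both arms, the bias is zero whatever the model.

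**The case against.** The strongest reply is that the plan does not compare the arms among scored children only. A reader might infer that from the choice of rater, but the Data analysis section extends multiple imputation to secondary outcomes, and only the complete-case sensitivity analysis is a subset comparison. A conservative imputation is also already promised, and its exact form may properly sit in an analysis plan that is not shown. Both points stand.

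A reader might also infer that FACAM will change daycare use. The documents do not show this. Registration guidance is one example within flexible support, CAU families may use daycare just as often, and no rates are given for either arm. Nor is the sign of any bias established.

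The figures rest on assumed inputs and describe an analysis that is not the main one. It would be wrong to judge them against the SMD of 0.33 in the sample-size section, which belongs to maternal sensitivity. Register outcomes at age 2 need no daycare rater.

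What the reply does not remove is the stated choice of predictors. Baseline data cannot carry a later daycare decision, and better child-level predictors are already collected.

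**Conclusion.** The point holds as a modest weakness in how one late secondary outcome is handled. SEAM depends on a post-randomisation state that FACAM may affect, and the stated baseline-only imputation may not remove the resulting bias if daycare use differs by arm.

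Under the assumed rates (80–90% against 90–95%) and a deficit of 0.5–0.8 SD, the bias in the complete-case contrast is about 0.03–0.09 SD, or 0.21–0.67 of a standard error. It is smaller in the imputed analysis to the extent that baseline is informative, and zero if uptake and the kinds of families using daycare match across arms. The documents support neither a claim that bias is present nor a claim about its direction. CIB maternal sensitivity at 12 months, the primary outcome, is untouched.

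**What to change.** 1. Record whether each child is in daycare when the teacher is sought at T4. This has to be found out anyway, and it separates having no teacher from a teacher who did not reply.
2. Report daycare enrolment and SEAM completion by arm.
3. Add ASQ:SE-2 (3 and 12 months), ASQ-3 (3 months) and Bayley (12 months) to the SEAM imputation model, and fit it by arm.
4. For SEAM, define the conservative imputation already planned as a delta shift for children not in daycare, with its size fixed in advance.
5. Label the complete-case SEAM comparison as conditional on a post-randomisation state.

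The shift should inform interpretation and should not become a pass-or-fail rule for claiming a SEAM effect, because any range chosen for it is itself an assumption.

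The cost is one status field, a somewhat larger imputation model, one defined sensitivity analysis and a more cautious SEAM statement. I would not rely on a separate T4 contact with mothers to collect the field: the Data collection section mentions a gift card at that age but schedules web surveys only at T0 to T3.
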